### Mental health messaging campaign

To support the Ahead of the Game program, a club-based promotional campaign was developed to improve mental health literacy to increase knowledge and attitudes about mental health and encourage help seeking in adolescent males (both for self and to help others). To inform, design and develop the campaign, a social marketing approach was utilised and included formative research, message development and concept pre-testing. Social marketing has been used successfully in a variety of health promotion interventions to increase awareness of health issues and promote behavior change [53]. In line with the CPBR framework, this requires meaningful involvement with the target audience to develop and design the intervention to ensure understanding of the relevant issue and associated behaviours. Thus the messages, concepts and promotional aspects for this campaign were developed based on the key insights from focus groups with adolescent males in the Illawarra. This included focusing on mental health to encourage help seeking with an emphasis on how to help others; including emotional and physical wellbeing to be consistent with the other components of the overall program; focusing on prevention and noting that sport/physical exercise impacts on both mental and physical wellbeing; addressing stigma around manliness, including showing or talking about feelings and emotions as well as beliefs about mental health issues resolving on their own without relevant help.

Three concepts were pre-tested to elicit views and understanding on images, taglines and messages. Based on the analysis, the final ‘Man Card’ concept (e.g., You won’t lose your Man Card for getting help) was chosen as the audience felt this would best resonate with their peers due to the use of humor, images being credible and relatable, but most importantly they felt that it had relevant and positive mental health messages. Final materials including posters, banners, branded merchandise and a campaign specific website will be disseminated across sports clubs in the Illawarra region in 2016/2017 to support the adolescent programs outlined previously.

### Control group

Participating clubs in the control group will not receive any program during the study period, but will be offered a mental health literacy program upon completion of the study. The INSIGHTS program is a community presentation aimed at teenagers and primarily delivered at secondary schools around Australia [Black Dog Institute, 2014. Accessed 01/10/2017. Available at: https://www.blackdoginstitute.org.au/education-training/community-and-schools/free-school-presentations/insights]. The presentations typically last an hour and are delivered by trained volunteers with personal experiences with mood disorders, who weave aspects of their story into the material presented. The presentation uses humorous illustrations to help explain concepts that young people find difficult to articulate and the topics covered include: pressures faced by teenagers today; signs and symptoms of depression and bipolar disorder in young people; identification of early warning signs; when and where to seek help; practical strategies for offering support; and strategies for building resilience.

### Measures

To measure mental health literacy, 13 items of the Depression Literacy Questionnaire [54], 13 items of the Anxiety Literacy Questionnaire [55], and one item from the Mental Health Literacy Scale, “I am confident that I know where to seek information about mental illness” [56] will be used. To measure help-seeking intentions, the General Help Seeking Questionnaire will be used [57] and to measure stigmatising attitudes, the Social Distance Scale will be used [58]. Items from the Mental Health Literacy Survey will also be included to investigate experiences with mental health, mental health first aid behaviours, and confidence to provide help [59]. If participants indicate that they have had contact with someone they believed to have a mental health problem, they will be asked if they tried to help, and are also asked to indicate what they did to try and help. In order to measure Mental Health First Aid intentions, participants will be asked to rate on a seven-point scale how likely they would be to do a list of five behaviours that is drawn from the content of the program. Items have been adapted from a previous measure [34]. Adolescent resilience will be measured using the 10-item version of the Connor-Davison Resilience Scale [60]. Implicit beliefs regarding one’s ability to deal with problems will be measured using three items adapted from previous research [61]. Perceived parental social support will be measured using the four items of the parental support subscale of Multidimensional Scale of Perceived Social Support [62]. In addition, parents’ are asked to report on 15 items of the Mental Health Literacy Scale (O’Connor & Casey, 2015).

To measure the effects of the coach education program we will use measures of athlete engagement, athlete burnout, perceived needs support, coach controlling behaviour, basic needs satisfaction, and self-determined motivation. Athlete engagement will be measured using the mean of four items measuring confidence, vigour, dedication and enthusiasm drawn from the Athlete Engagement Questionnaire [63]. Athlete burnout will be measured using the mean of three items assessing emotional and physical exhaustion, devaluation, and reduced sense of accomplishment drawn from the Athlete Burnout Questionnaire [64]. Perceived needs support will be measured using the mean of three items assessing autonomy, competence and relatedness drawn from the Perception of Needs Support Scale [51]. Controlling coach behaviour will be measured using the mean of four items drawn from the Controlling Coach Behaviour Scale [65] measuring controlling use of rewards, negative conditional regard, intimidation, and excessive personal control. Satisfaction of basic needs will be measured using five items drawn from the Basic Need Satisfaction in Sport Scale [66]. Three items will be used to measure autonomy, and one item each to measure competence and relatedness. Self-determined motivation will be measured using five items drawn from the Behavioural Regulation in Sport Questionnaire [67], with items measuring amotivation, external regulation, introjected regulation, identified regulation, and intrinsic motivation.

To explore potential effects of the program on adolescent males’ mental health and wellbeing, two measures are used. Psychological distress is measured using the Kessler-6 (K6); [68], a six-item questionnaire assessing the level of depressive and anxiety symptoms that have been experienced within the past month. Wellbeing is measured using the short form of Keyes’ Mental Health Continuum (MHC); [69]. This is a 14-item measure of an individual’s emotional, psychological and social wellbeing. The short form of the MHC has shown excellent internal consistency (> .80) and discriminant validity in adolescents. All measures will be taken at three time points: (i) prior to commencement of participation in Ahead of the Game programs, and as close to the start of the sporting season as possible; (ii) immediately following participation (i.e., post workshop); and (iii) six weeks after last involvement with Ahead of the Game, or immediately prior to the end of the sporting season, whichever is longer.

To supplement quantitative measures, qualitative evaluation of all intervention components is planned to obtain a richly textured, detailed understanding of the project from the perspective of participants. This qualitative component moves beyond the measures chosen by researchers to provide stakeholders with an opportunity to express their own perceptions and experiences of the programs. Specifically, focus groups and interviews are employed to understand the perceptions and experiences of adolescents, coaches, and parents regarding intervention programs. This component of the evaluation is expected to generate new insights into ‘what works’ and ‘what doesn’t work’ from the perspectives of those who have undertaken the program.

### Recruitment and engagement strategy

The project engagement strategy is informed by the guiding principles outlined in the Stakeholder Engagement Framework (e.g. reciprocity, inclusion, transparency, and respect) [70], in keeping with our CBPR priorities. The engagement strategy has three phases. Phase 1 – Building awareness: Key messages are developed concerning the need for and timeliness of the project, as well as the involvement of the Illawarra community in developing Ahead of the Game interventions. These particularly emphasise gains for the club and the mutually beneficial nature of involvement for all stakeholders [71]. Public awareness of the project is through disseminating key messages primarily with local and online media in the first instance, followed by dissemination via the project website, social media accounts, community presentations, and leveraging the capacity of partner organisations. Phase 2 – creating relationships with key stakeholders: Strategic partnership opportunities will be identified by scoping the organisations and/or peak bodies at national, state and local levels with the capacity to connect Ahead of the Game directly with local clubs across the six sports. The research team directly approach identified organisations to gain their support and ascertain their willingness to facilitate recruitment. Where possible, opportunities for identifying ambassadors, attending club meetings and generating media coverage are explored. All partner organisations are then listed on the official project website. Phase 3 – Recruitment of community clubs: Building on public awareness of the project generated in Phase 1, all sports clubs in the Illawarra and Central Coast regions are invited to participate in the Ahead of the Game trial. Clubs are notified about the project prior to the season starting, firstly by email/newsletter contact from governing bodies and invited presentations at all-clubs meetings, and secondly, in writing (email or letter directed to the club president) by the research team. Clubs will be offered individual club presentations on an as needed basis. Additionally, individuals will be able to fill in an expression of interest via the website.

To maximise consent rates, club engagement officers will be employed to liaise and follow up with all invited clubs, using scripted telephone calls and engagement checklists. At the point of recruitment club representatives will sign a letter of support indicating their commitment to implementing the program and appoint a club-level ‘champion’ for the duration of the project. Throughout the engagement process, the team will document stakeholders’ motivation to engage or disengage with the goals of the project.

### Sampling and recruitment of participants and stakeholders for qualitative evaluation

Interviews and focus groups will take place with purposively sampled participants and sporting organisation stakeholders (e.g., club presidents, player development coordinators) approximately a month after the final questionnaire. Adolescent participants will be recruited through their teams/groups (i.e., for focus groups), while parents and coaches will be recruited individually (i.e., for interviews). All individuals who participated in the program will be invited to take part in interviews or focus groups, regardless of the extent to which they completed the program (in order to facilitate a maximum variation sample). Those selected for interviews/focus groups will be sent an additional participant information sheet and consent form by the research team. Data will be collected until saturation is reached. The interviews and focus groups will explore acceptability of the intervention and research design, perceived impact of the intervention, and strategies for refinement and dissemination.

### Implementation strategy

We will aim to engage in a scientifically grounded implementation strategy for this multi-setting, multicomponent, multi-level intervention. As with most mental health interventions, successful implementation requires an interaction among multiple individuals, organisations, funders, and systems to be successful, thus making interventions highly complex to implement. The aim of the implementation strategy is to effectively promote adoption of intervention components. Implementation of evidence-based and evidence-informed practices in mental health is critical for improving health outcomes. The strategy is informed by two implementation frameworks– the National Implementation Research Network (NIRN) model of implementation and the Consolidated Framework for Advancing Implementation Research (CFIR) [72, 73]. These conceptual models are complementary; the NIRN model [73] characterises the overarching staged processes of implementation and key drivers for successful implementation, while the CFIR model explores the role of various constructs at multiple levels of influence [72].

### Sample size calculations

To calculate the required sample size we have used the general indicator of psychological distress (K6) rather than other program specific outcomes. Based on pilot testing using two independent samples with a between group difference of 1.2 (*SD* = 4.0), adjusting for clustering using a design effect of 1.35 it is estimated that 231 subjects are required in each group (with an alpha of 0.05 and 80% power).

### Qualitative evaluation sample size

The qualitative evaluation will collect data until saturation is reached. We anticipate that up to 50 adolescent participants, 20 parents, and 10 coaches will be included.

### Data analysis

#### Analyses of primary and secondary outcomes

Between-group differences on the primary and secondary outcomes will be analysed according to both intention-to-treat and per-protocol principles, using appropriate multivariable statistics (linear mixed models, generalised linear models adjusting for clustering and covariates such as age and socioeconomic status).

#### Mediation and moderation analyses

Two analyses will be conducted to explore potential mediators and moderators of the intervention effects. First, hypothesised mediators of change in primary outcomes (e.g., mental health literacy) will be examined. Potential moderators of the intervention effects (e.g., socioeconomic status, age, and geographic location) will also be explored using multi-level modelling.

#### Per-protocol analyses

A per-protocol or dose-response analysis will also be performed at the club and individual levels. Adolescents’ individual-level compliance will be measured using the following indicators: having a coach who completes the coach training program; a club who implements the messaging campaign; at least one parent who has received the parent program; attendance at the Help Out a Mate program; and, attendance at the Your Path to Success in Sport program. All participants and clubs will be included in the intention-to-treat analyses.

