### Aims and hypotheses

The primary research questions are as follows:What effect does the intervention have on adolescent mental health literacy, intentions to seek and provide help, and stigmatising attitudes?What effect does the intervention have on adolescent resilience?What effect does the intervention have on adolescent self-determined motivation?What effect does the intervention have on parents’ mental health literacy and confidence to seek help?

We hypothesise that, compared with adolescents in a control community, adolescents who participate in the intervention will show increases in mental health literacy, intentions to seek and provide help, and a decrease in stigmatising attitudes. We also hypothesise that adolescents who participate in the intervention will show increases in resilience, while those whose coaches participate will also show increases in perceived need support and self-determined forms of motivation. We hypothesise that parents who participate will show increases in mental health literacy. Furthermore, we expect that any potential intervention effects will be moderated by baseline mental health and wellbeing, with greater effects for those who report lower levels of mental health and wellbeing at baseline.

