### Intervention components

There are four intervention components and a supplementary messaging campaign. Participants will be invited to participate in all relevant programs, but will be able to choose which programs they attend. Attendance at any given program is not dependent upon attendance of another.

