The internet-based component of the intervention is delivered via website and/or mobile phone application. The website is accessible on any internet-enabled device, and the app is available to download on mobile devices. Each of the six core modules takes approximately 10–15 min to complete, and they are designed to be completed in order (i.e., the first module had to be completed before the second was unlocked). Informed by sport-based resilience literature (see above), the modules are: (i) problem-solving; (ii) controlling the controllables; (iii) managing your thoughts; (iv) keeping your cool; (v) playing to your strengths; and (vi) appreciating your team. An additional recap module was also available to participants who completed all six preceding modules (e.g., with summary material and evaluative questions). Participants will be able to complete all modules in one session if desired, however the content is designed so that participants can continue to engage with and practice the exercises after all modules were completed. These skills are delivered through informational videos, infographics, reflective activities, and exercises to try at the end of each module. This component of the intervention will be delivered individually, and participants are required to log in to access the materials. The hypothesised outcomes of the program are more adaptive implicit beliefs about managing adversity, and increases in resilience.

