## Discussion

This study utilises a community-based participatory research framework to test a multi-level, multi-component intervention designed to enhance mental health and wellbeing and reduce the risk of the mental health problems among adolescent males who participate in organised sports. The intervention will be implemented at a community level and will be tested against a matched case control community. Specifically, the intervention targets adolescents, as well as their peers (teams), parents, coaches, and the sporting environment by embedding four programs and a complimentary messaging program within community sporting clubs. The dual foci of the program are the explicit and intentional promotion of protective factors in addition to harm-reduction strategies. Protective factors include high levels of psychological well-being, high levels of social support, and self-determined forms of motivation. Early intervention and harm reduction strategies include high levels of mental health literacy, intentions to seek and provide help for emerging mental health problems, and knowledge of options for professional help.

Organised sports are a promising avenue for mental health promotion, particularly among adolescent males. High participation rates and prolonged engagement in organised sports make them conducive to the delivery of programs such as Ahead of the Game [17, 18]. In considering study limitations we note that intervening in a sample of sports participants presents a risk of bias to the study given that sports participation is associated with better mental health and non-participation is associated with higher risk for mental health problems [20]. As such, those who are most in need of intervention may not be systematically exposed to any program which is implemented solely through community sporting clubs. Furthermore, the multi-level design could be expected to lead to greater change in primary outcomes, as well the maintenance of potential benefits. However, the multi-level design may enhance a form of self-selection bias whereby adolescents with strong social support systems may be more likely to participate and more likely to have coaches, parents, and peers who also participate. This is particularly relevant for per-protocol analyses.

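### The per-protocol comparison is open to self-selection that the plan acknowledges but does not handle, so it could show benefit from an inert programme; separately, the resilience dose ignores the online modules

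*Protocol article*

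**What the plan says.** All references are to the protocol article.

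- **Standing of the analyses.** Under Analyses of primary and secondary outcomes, between-group differences "will be analysed according to both intention-to-treat and per-protocol principles". Neither is called primary. Per-protocol analyses adds: "A per-protocol or dose-response analysis will also be performed at the club and individual levels". That section also keeps every participant and club in the intention-to-treat analysis.
- **Hypotheses.** Aims and hypotheses words the expected effects on people who take part, for example that "those whose coaches participate will also show increases in perceived need support and self-determined forms of motivation".
- **Who attends.** Under Intervention components, participants "will be able to choose which programs they attend". Under Control group, control clubs get no programme until the study is over.
- **Compliance.** Per-protocol analyses lists five individual-level indicators: a trained coach, a club running the messaging campaign, a parent who received the parent programme, and attendance at each of the two adolescent programmes. For resilience the indicator is "attendance at the Your Path to Success in Sport program".
- **Adjustment.** The models named include "generalised linear models adjusting for clustering and covariates such as age and socioeconomic status".
- **Acknowledged bias.** The Discussion says that "adolescents with strong social support systems may be more likely to participate and more likely to have coaches, parents, and peers who also participate", and that this matters especially for the per-protocol analyses.
- **Resilience programme.** It has one workshop of about 45 minutes and six online modules of 10 to 15 minutes each, unlocked in order. For the online part, "participants are required to log in to access the materials".

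**The concern.** A per-protocol contrast between communities is fair only if boys who comply in the intervention community have the same prognosis as the boys they are compared with. Here compliance is a choice, and it can be observed on one side only. The article supplies both links of a confounding path: the Discussion says that strong social support may raise participation, and it also lists social support among the protective factors. One indicator, a parent who came to the parent programme, selects on parental engagement directly. If attenders would have done better anyway, that head start is read as a programme effect. Because the two principles are unranked and the hypotheses are worded on participants, a favourable per-protocol result could be presented as the answer to the primary question.

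The second issue is separate. If attendance is the only resilience indicator, a boy who came to the workshop and never opened a module may count as compliant. Dose is then misclassified in the programme that delivers most of its content online.

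**Working it through.** **1. The plan's own figure.** Sample size calculations gives a K6 difference of 1.2, SD 4.0, alpha 0.05 (two-sided assumed), 80% power and a design effect of 1.35. Then n = 2 × (4.0 × (1.960 + 0.842) / 1.2)² = 174.4 per group, and 174.4 × 1.35 = 235.5. The stated 231 is within 3% of this (power at 231 is 79.2%), so its inputs can be used. The planning effect is 1.2 / 4.0 = 0.30 SD. K6 serves here only as a scale, since the article treats effects on distress as exploratory.

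**2. Bias with an inert programme.** Assumptions, none given in the article: a share p of the 231 intervention boys attend; they are the top p of a latent propensity to attend; that propensity correlates ρ with a favourable outcome; the true effect is zero; and follow-up scores are compared without adjustment.

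- Shift in SD = ρ × φ(z) / p, with z the normal quantile that cuts off p. At p = 0.5 this is ρ × 0.399 / 0.5: 0.16 for ρ = 0.2 and 0.24 for ρ = 0.3, or 53% and 80% of 0.30 SD.
- SE = √(1.35 × (1/(231p) + 1/231)). At p = 0.5 this is √(1.35 × (1/115.5 + 1/231)) = 0.132.
- False benefit = P(Z > 1.96 − shift/SE), nominally 2.5%.

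| Attend | Shift (SD), ρ = 0.1 / 0.2 / 0.3 | False benefit | False harm at ρ = −0.2 |
|---|---|---|---|
| 30% | 0.12 / 0.23 / 0.35 | 11% / 31% / 59% | 31% |
| 50% | 0.08 / 0.16 / 0.24 | 9% / 23% / 44% | 23% |
| 70% | 0.05 / 0.10 / 0.15 | 6% / 13% / 24% | 13% |

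At ρ = 0 the false-benefit rate stays at 2.5%. At ρ = −0.2 (boys in greater need attend) it is 0.3% or less.

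**3. Effect of adjusting for the baseline outcome.** Simulation at 50% attendance, with an assumed baseline to follow-up correlation of 0.6:

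- If selection acts only through the measured baseline, the adjusted shift is essentially zero (−0.001 to 0.002 SD).
- If selection acts through a stable trait, the shift falls from 0.156 to 0.064 SD (ρ = 0.2) and from 0.236 to 0.096 SD (ρ = 0.3). With SE = 0.132 × √(1 − 0.6²) = 0.106, false benefit is about 9% and 15%.

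**4. Resilience dose.** Online time is 6 × 10 to 6 × 15 = 60 to 90 minutes. With the 45-minute workshop the total is 105 to 135 minutes. The online share is 60/105 = 57% to 90/135 = 67%.

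**The case against.** A reader might infer that the per-protocol analysis *would* show benefit from an inert programme. The article does not support that. Attendance and ρ are assumed. Even with favourable selection, false benefit runs from 6% to 59%, mostly below half. The Discussion says only that supported boys *may* participate more; it gives no size and no net direction for each outcome. That stronger reading fails.

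The 23% to 44% also describe an unadjusted, follow-up-only contrast. Outcomes are measured at baseline, mixed models are planned, and the covariate list is open. A baseline term is therefore not excluded, and its detail may sit in an analysis plan that is not shown. This stands as a limit on the size. It does not remove the point, because the article names the bias and then names no covariate that bears on it.

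The comparator is inferred. The wording leaves per-protocol or dose-response open and sets no comparison set, although attenders against all controls is the natural reading of a between-group per-protocol analysis. A dose-response analysis within the intervention community is also permitted, but self-selection persists there.

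Nor are controls unselected: their clubs also agreed to take part. They are unselected only for programme attendance.

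Finally, a reader might infer that counting attendance alone adds to false benefit. It does not: misclassified dose usually dilutes a real effect and cannot create one. It could also be said that the indicator refers to the programme as a whole, but attendance most naturally means the workshop, and module completion is not listed.

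**Conclusion.** The point holds as two separate weaknesses of an analysis that the article leaves unranked against intention-to-treat.

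First, the per-protocol comparison *could* show benefit from an inert programme. The size is conditional: 0.16 to 0.24 SD and 23% to 44% false benefit without adjustment, at 50% attendance and ρ of 0.2 to 0.3. With baseline adjustment it ranges from essentially no bias to 0.06 to 0.10 SD, depending on how selection works. The direction reverses if boys in greater need attend.

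Second, attendance as the only resilience indicator leaves 57% to 67% of core programme time out of the dose. This blurs dose-response and dilutes any real effect.

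Because intention-to-treat on all participants and clubs is retained, the per-protocol result is not the only evidence. These changes should be made, but the trial's conclusions need not rest on the flawed contrast.

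**What to change.** 1. Name intention-to-treat by community as the primary analysis, and reword Aims and hypotheses so that the hypotheses refer to that comparison rather than to those who take part.
2. Label the per-protocol or dose-response analysis supportive and associational, and state which boys are compared with which.
3. Adjust it for the baseline value of the outcome, baseline K6, baseline wellbeing and baseline perceived parental support. The Measures section already has all of these collected before participation.
4. Use the number of modules completed (0 to 6) alongside workshop attendance as the resilience dose. Log-in and sequential unlocking imply that completion is tracked per boy; confirm that the record is kept.

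The cost is a little more analysis work and no new measures. Residual self-selection remains. Replacing the control contrast with an analysis inside the intervention community only is a trade-off, not a cure: it uses about half the sample and still compares boys who chose differently.
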